### Outcome measures

The following clinical scores and questionnaires, as well as blood analyses, will be collected at all three visits (V1, V2, V3) and compared over time:

Clinical scores:Inflammatory Rasch-built Overall Disability Scale (I-RODS)Inflammatory Neuropathy Cause and Treatment (INCAT) disability scoreGrip strengthMedical Research Council (MRC)-Sumscore
Questionnaires:Subjective occurrence of end-of-dose phenomena/wearing offAbbreviated World Health Organization Quality of Life (WHOQOL-BREF)Pittsburgh Sleep Quality Index (PSQI)
Blood analyses:Levels of sNfLSerum proteomics and metabolomics

A questionnaire on smartwatch use containing the System Usability Scale will additionally be asked at the final visit (V3).

Over the entire period of 6 months, the following outcome measurements will be recorded with the Withings ScanWatch:Wearing time of smartwatch (daily)Longitudinal development of activity parameter: step count, approximate distance traveled (meter), duration of soft, moderate, and intense activity (seconds) defined by Withings, the sum of all active time (seconds), approximate calories burnedLongitudinal development of sleep parameter: time awake (seconds), number of times user woke up, time to sleep (seconds), total time in bed (seconds), total time asleep (seconds), ratio of sleep/ time in bed, time spent in bed before falling asleep (seconds), time awake after first falling asleep (seconds), Withings Sleep score defined by WithingsLongitudinal development of cardiovascular parameters: average heart rate, maximal heart rate, minimum heart rate, time in light, moderate, intense, and maximal heart rate zone (seconds) defined by WithingsLight heart rate zone: from 0% inclusive to 50% exclusive of maximum heart rate. Moderate heart rate zone: from 50% included to 70% excluded of maximal heart rate. Intense heart rate zone: from 70% included to 90% excluded of maximal heart rate. Maximal heart rate zone: from 90% included to 100% included of maximal heart rate.Number and time of irregular 1-channel ECGs (according to Withings algorithm)

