**Methods:**

In this prospective, observational, non-interventional, single-center, investigator-initiated study, CIDP patients treated with IVIG will be continuously monitored over a period of 6 months. Clinical scores and blood analyses will be assessed and collected during three visits (V1, V2, V3). Additionally, activity, sleep, and cardiac parameters will be recorded over the entire period using a wearable device. Further, patients' subjective disease development and quality of life will be recorded at various visits (read-outs). The usability of the smartwatch will be assessed at the end of the study.

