### Study description and study design

This prospective, observational, non-interventional, single-center, investigator-initiated study is being conducted at the University Hospital of Düsseldorf, Germany.

Upon introduction to the trial and written consent, CIDP patients treated with IVIG are enrolled in the study during the screening visit in conjunction with the baseline visit (V1). During this onsite visit participants are handed out a wearable (ScanWatch, Withings, Paris, France) and instructed in the use of the technology. After a 1-week period, a phone visit will be conducted to clarify any technical issues. Wearables are used to continuously record patients' activity, cardiac, and sleep parameters for a total of 6 months. In addition, a second onsite visit (V2) is scheduled after 3 months, and a final visit (V3) after 6 months. At all three onsite visits, clinical examinations, scores to classify CIDP-related symptom severity, and questionnaires regarding quality of life, quality of sleep, and the subjective occurrence of end-of-dose phenomena will be collected. In addition, a serum sample will be collected to analyze markers of neuroaxonal damage such as serum neurofilament light chain (sNfL). Furthermore, we aim to employ non-targeted proteomics to systematically analyze protein expression patterns in CIDP patient samples, aiming to identify potential biomarkers or therapeutic targets. By combining this comprehensive proteomic data with digitally captured behavioral information, we seek to uncover novel insights into proteomic-behavioral interactions in CIDP patients, ultimately improving disease understanding and facilitating personalized treatment strategies (see Fig. 1).

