**Fig. 1 Fig1:**
[figure not shown]
Graphical outline of the study protocol. *IVIG* intravenous immunoglobulins

Throughout the period, patients will receive their regularly scheduled IVIG infusions.

Sample size calculation: Given the exploratory and observational nature of our study, we do not have a specific hypothesis to test, making power analysis less suitable in this context where basic information on distributions is currently missing. The primary objective is to generate first-hand data to enable hypothesis formation and identify potential relationships for further examination in subsequent hypothesis-driven studies.

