### Arms and interventions

As this is an observational cohort study, there are neither interventions nor arms. Patients will be stratified by their biological and digital behavioral phenotypes retrospectively to assess differences in disease activity patterns.

It is planned to enroll approximately 60 patients in the study.

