### Eligibility criteria

CIDP patients treated with IVIG in constant intervals are included.

Further inclusion criteria are:Age ≥ 18 yearsProbable or definite CIDP patients according to the European Federation of Neurological Societies/Peripheral Nerve Society 2010 criteria [16].IVIG treated as follows:Documented evidence of objective response to IVIG, with clinically meaningful improvement. Clinically meaningful improvement is defined as one of the following: ≥ 1 point decrease in adjusted INCAT score, ≥ 4 points increase in I-RODS total score, ≥ 3 points increase in MRC Sum score, ≥ 8 kilopascal improvement in mean grip strength (one hand), or an equivalent improvement based on information documented in medical records and per the principal investigator's (PI) judgement.Must be on stable IVIG therapy, defined as no change greater than 10% in frequency or dose of immunoglobulin therapy or corticosteroids within 8 weeks prior to screening.Evidence of clinically meaningful deterioration on interruption or dose reduction of IVIG therapy within 24 months prior to screening, determined by clinical examination or medical records. Clinically meaningful deterioration is defined as one of the following: ≥ 1 point increase in adjusted INCAT score, decrease in I-RODS total score ≥ 4 points, decrease in MRC Sum score ≥ 3, mean grip strength worsening of ≥ 8 kilopascals (one hand), or an equivalent deterioration based on information from medical records and at the PI's judgement.

The exclusion criteria are:unable to use smartwatch or/ and smartphone device

To maximize recruitment potential in a rare disease and minimize bias in this real-world measurement cohort, other comorbidities are not considered causes for exclusions. While this might be a source of potential error, we assess patients at every visit for comorbidities or special life events to best correct for effects on intra-patient measurements.

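### The System Usability Scale is scheduled only at V3, so patients who withdraw earlier give no usability score and the V3 result may be too favourable

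*Protocol article*

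**What the plan says.** Under Outcome measures, the protocol article lists the clinical scores, questionnaires and blood analyses collected at V1, V2 and V3, and then adds one item for the last visit only: "A questionnaire on smartwatch use containing the System Usability Scale will additionally be asked at the final visit (V3"). The Methods paragraph of the Abstract agrees: "The usability of the smartwatch will be assessed at the end of the study".

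Four other statements bear on the point:

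- **Visits** (Study description and study design): "a second onsite visit (V2) is scheduled after 3 months, and a final visit (V3) after 6 months". An earlier contact is by telephone: "After a 1-week period, a phone visit will be conducted to clarify any technical issues". Neither the call nor V2 is said to carry a usability score.
- **Entry** (Eligibility criteria): the only listed exclusion is "unable to use smartwatch or/ and smartphone device".
- **Record of use** (Outcome measures): the first watch-derived outcome is "Wearing time of smartwatch (daily"), recorded over the whole 6 months.
- **Size** (Arms and interventions): "It is planned to enroll approximately 60 patients in the study". There is no power calculation; the sample size paragraph explains that "we do not have a specific hypothesis to test, making power analysis less suitable in this context".

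**The concern.** A usability score taken only at the last visit describes the patients who reach that visit. The study asks for continuous wear over 6 months, and the Introduction names distal paresis and sensory disturbance among the typical symptoms of the disease. Trouble handling the watch, or the burden of wearing it, is therefore a plausible reason to leave the study. If so, whether a score is missing depends on the quantity being measured, and the average among V3 attenders is too favourable.

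What is at stake is modest. Usability is one descriptive item in a hypothesis-generating study. Still, anyone planning a later study with the same device would take the score as it stands, and a rating not obtained when a patient leaves is hard to recover afterwards.

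**Working it through.** **Inputs from the protocol article.** Planned enrolment is about 60; the usability questionnaire is at V3 only; V2 is at 3 months and V3 at 6 months. No dropout rate, expected usability mean or standard deviation is stated, so there is no figure of the plan's own to reproduce.

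**Assumptions (not in the article).** Share of enrolled patients missing at V3: 5% to 30%, that is 3 to 18 of 60. Gap, meaning the mean score of V3 attenders minus the mean score that those missing would have given: 10 to 30 points.

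**Formula.** The mean for all patients is (1 − m) × attender mean + m × missing mean, where m is the share missing at V3. Subtracting this from the attender mean gives

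overstatement = m × gap.

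| Missing at V3 | Gap 10 | Gap 20 | Gap 30 |
|---|---|---|---|
| 5% (3 of 60) | 0.5 | 1.0 | 1.5 |
| 10% (6 of 60) | 1.0 | 2.0 | 3.0 |
| 20% (12 of 60) | 2.0 | 4.0 | 6.0 |
| 30% (18 of 60) | 3.0 | 6.0 | 9.0 |

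**Stopping the watch is not the same as missing V3.** Assume 12 of 60 patients stop wearing the watch, their scores are 20 points below those of the other 48, and all 48 attend V3. Relative to those 48, the mean for all 60 patients is −(12 × 20)/60 = −4.0. If a of the 12 attend V3 and answer, the observed mean is −20a/(48 + a), and the overstatement is the observed mean minus −4.0:

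| Stoppers who attend V3 | Observed mean | Overstatement |
|---|---|---|
| 0 | 0 | 4.0 |
| 6 | −120/54 = −2.2 | 1.8 |
| 10 | −200/58 = −3.4 | 0.6 |
| 12 | −240/60 = −4.0 | 0 |

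With the number of stoppers held at 12, the overstatement runs from 4.0 points to nothing, depending only on V3 attendance.

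**After the change.** The same arithmetic applies to scores obtained at withdrawal. If all 12 are absent from V3 but all give a score on leaving, the overstatement due to missing scores is 0. If 6 of the 12 do, 1.8 points remain. This treats the score given on leaving as the score that would have been given at V3.

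**The case against.** The strongest case on the other side has four parts.

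1. **Non-wearers can still be asked.** A reader might infer that patients who stop wearing the watch are not counted, so that usability is bound to be overstated. The article does not support this. It nowhere says that a non-wearer is withdrawn, skips V3 or is left out of the questionnaire. V3 is an onsite visit with examinations, scores, questionnaires and a serum sample, none of which needs the watch. A patient who gave it up in month 2 can attend and give a poor rating. This stands, and it limits the point to patients missing at V3.

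2. **Related information is collected.** Daily wearing time records reduced or stopped use objectively, and the call after one week deals with technical trouble. This stands in part: wearing time shows that use stopped but not why, so it complements a usability score without replacing one.

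3. **The full protocol may cover withdrawal.** Procedures at early termination are often left out of a journal article, and their absence here is not held against the plan. The point rests on what the article does state, in two places: a single assessment at the end.

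4. **The item is minor.** The Perspective section says that digital monitoring may be extended beyond specialised centres, but it does not rest that on the usability score. A reader might treat the score as the evidence for such an extension; the text does not make that link. This stands and keeps the point small.

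The exclusion of patients unable to use the device is a separate matter. It is openly stated and understandable in a study whose data come from the watch. It defines the patients to whom a usability result applies and is not a consequence of asking at V3.

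**Conclusion.** The point holds as a conditional one. The usability questionnaire is fixed at V3 only, so a patient who leaves before month 6 has no score under the published schedule, and the result among attenders may be too favourable. The direction depends on withdrawal being related to difficulty with the watch; if withdrawal is unrelated to usability, the gap is zero and so is the bias.

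The range of 0.5 to 9 points rests wholly on the two assumed inputs and is an illustration, not an estimate. Zero is also possible, namely when all who stop wearing the watch attend V3 and answer. The shortcoming affects one descriptive outcome and leaves the study's main aims untouched. It is worth correcting because doing so is cheap.

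**What to change.** Give the same questionnaire at three occasions:

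- at V2, which is already an onsite visit;
- at early withdrawal from the study or permanent stop of watch use, by telephone if needed, which also reaches patients who leave before month 3;
- at V3, with an explicit statement that it is asked whether or not the watch is still worn.

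Keep the V3 score as the main usability result. Add a sensitivity summary that includes the last available score of patients who did not attend V3. Report both beside daily wearing time, the number of V3 non-attenders with reasons, and the number excluded at screening as unable to use the device.

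The cost is a few minutes of questionnaire time at an existing visit or one telephone call, with no new instrument. The drawback is that the sensitivity summary mixes ratings given after different lengths of use, which is why it should not replace the V3 result.

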## Introduction

Chronic inflammatory demyelinating polyneuropathy (CIDP) is one of the most common immune neuropathies [11]. It is characterized by a progressive or relapsing disease course developing for more than 8 weeks, often leading to severe restriction of the patient's everyday life [5, 14]. Typical symptoms are symmetrical distal and proximal paresis, sensory disturbances, and reduced to absent reflexes. Therapeutic long-term options, in addition to glucocorticoids and plasma exchange, are mainly intravenous immunoglobulins (IVIG) (Van den [16], which must be administered repeatedly to ensure disease stability [9]. As typical intervals between IVIG applications range from 4 to 12 weeks, individual interval finding is sometimes difficult in the context of CIDP. In daily routine, treatment intervals primarily rely on clinical examinations, which frequently struggle to quantify patients' fluctuating deficits effectively. Alternatively, slight changes relevant to patients’ everyday lives are sometimes taken as indicators and lead to alterations of the individual dosing interval. Therefore, the subjective perspective of patients is even more relevant for the adjustment of the therapy intervals.

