## Methods

### Aim of the trial

The goal of the EMDA CIDP study is to evaluate various widely available smartwatch-derived digital metrics and blood-based analyses for monitoring disease activity in CIDP patients treated with IVIG.

First, digital and blood-based measurements will be compared with subjective patient reports and established clinical scores. Second, exploratory analyses aim to understand longitudinal disease progression and its variability in individual patients. Thus, by monitoring a variety of digital and biological phenotypes of CIDP patients, individual determinants and measurements of disease activity patterns will be explored and characterized. Novel auspicious combinations of disease activity measurements may improve dose and interval optimization in the future. Considering the influence of behavioral traits such as physical activity and sleep on patients' metabolic state and various bodily functions [8, 10], we aim to explore the interplay between behavioral and biomedical characteristics in our patients. By monitoring both behavioral and biomedical parameters over time, we further aim to investigate the potential response of biomedical features to changes in activity or sleep patterns.

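### Step count and distance from a watch are correlated with disability scores across patients, with walking-aid and wheelchair users eligible; if the watch misses steps in aid users, the pooled correlation is created or inflated.

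*Protocol article*

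**What the plan says.** All passages are in the protocol article.

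- **Device and outcome.** Under Study description and study design, "participants are handed out a wearable (ScanWatch, Withings, Paris, France"); no other activity sensor is named. Under Outcome measures, the watch supplies "step count, approximate distance traveled (meter") among the activity parameters. The clinical comparators listed there are I-RODS, the INCAT disability score, grip strength and the MRC sum score.
- **Population.** The Introduction states: "Typical symptoms are symmetrical distal and proximal paresis, sensory disturbances, and reduced to absent reflexes". Under Eligibility criteria the sole exclusion is being "unable to use smartwatch or/ and smartphone device", and "other comorbidities are not considered causes for exclusions".
- **Use.** Under Aim of the trial, "digital and blood-based measurements will be compared with subjective patient reports and established clinical scores". Analysis strategy adds correlation of clinical and digital parameters at baseline and for longitudinal change. It also plans repeated comparison of digital measures between points of the treatment cycle, such as the first week after an infusion against the week before one.
- **Safeguard.** Eligibility criteria concedes that broad entry may bring error and answers: "we assess patients at every visit for comorbidities or special life events to best correct for effects on intra-patient measurements". Mobility aids are not named.

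**The concern.** A wrist sensor infers walking from arm movement. A patient whose hand rests on a cane, walker or wheelchair moves about with less arm swing, so the watch may record fewer steps than were taken. Undercounting at random would only weaken a correlation. Undercounting that is concentrated in the more disabled patients pushes the correlation in the direction that would be read as support for the watch.

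The first aim is to set digital measures against clinical scores. A pooled correlation of steps with INCAT or I-RODS could therefore be taken as evidence that the watch tracks disease activity when part of it is measurement error. The study exists to select candidate markers for later hypothesis-driven studies, so an artefact could be carried forward. The stated safeguard does not reach this: a walking aid needed because of CIDP is neither a comorbidity nor a life event, and the correction is aimed at measurements within a patient, whereas the bias is largest between patients.

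**Working it through.** The article has no figure to reproduce. It plans about 60 patients, declines a power calculation, and gives no step-detection error and no share of aid users. The check is therefore a simulation over assumed ranges.

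**Inputs**
- From the article: n = 60.
- Assumed: share of aid users p; share m of an aid user's steps that the watch misses; true steps log-normal with SD 0.5 on the log scale; leg score 0-1 without an aid and 2-4 with one. That INCAT grades the legs by walking aid is also an assumption, since the article does not describe its items.

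**Formula.** Observed steps = true steps × (1 − m) for aid users, and true steps for the rest. On the log scale aid users shift by ln(1 − m): −0.11 at m = 0.1, −0.36 at 0.3, −0.69 at 0.5 and −1.20 at 0.7, against an SD of 0.5.

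**Step 1: true steps unrelated to disability, p = 20%, 4,000 simulated cohorts.** Mean Spearman correlation of observed steps with the score:

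| Steps missed | Leg-only score | Leg score plus independent arm score (0-4) |
|---|---|---|
| 0% | 0.00 | 0.00 |
| 10% | -0.06 | -0.04 |
| 30% | -0.19 | -0.13 |
| 50% | -0.34 | -0.23 |
| 70% | -0.46 | -0.31 |

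The correlation passes a two-sided 5% threshold in about 7% of cohorts at 10% missed with the leg-only score, hardly above the nominal rate, and in about 95% at 70% missed. With the arm part added, the share at 70% missed is about 69%. The negative sign is for a score that rises with disability, as INCAT does; it reverses for I-RODS, MRC and grip strength.

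**Step 2: looser link between aid use and disability** (latent correlation 0.7, coefficient of variation of true steps 0.5). At p = 20%, missing 20/40/60/80% of steps gives -0.08/-0.18/-0.27/-0.33. At p = 10% the range over the same miss rates is -0.05 to -0.19; at p = 40% it is -0.12 to -0.47.

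**Step 3: true steps do fall with disability** (assumed 0.2 log units per leg-score point, p = 20%, leg-only score). The correlation is -0.38 with nothing missed and -0.50 with 30% missed. Here the error inflates a real association.

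**Step 4: unaided walkers only.** With no true association, the correlation returns to about 0 at every miss rate. With the true association of Step 3, it is about -0.19 instead of -0.38, because the range of the score has been cut.

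**Step 5: within-patient contrast.** Let u be the share of walking done with an aid. With no true change in walking, the observed end-to-start ratio is (1 − m·u_end)/(1 − m·u_start).
- Constant aid use: the ratio is 1.00 and the error cancels.
- Aid use rising from 30% to 50% of walking: m = 0.2 gives 0.90/0.94 = 0.96; m = 0.4 gives 0.80/0.88 = 0.91; m = 0.6 gives 0.70/0.82 = 0.85. That is an apparent fall of 4% to 15%.

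**The case against.** The strongest reply is that the decisive links lie outside the article. Nothing in it says how well this watch counts steps with an aid, how many patients use one, or how INCAT grades the legs. With few aid users or a low miss rate the effect is negligible, as the 10% row shows. This stands, and it is why the size can be given only as a range.

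Second, independence of true steps and disability is an extreme case in a disease of limb paresis. This also stands: the likelier harm is inflation (Step 3). A reader might infer that any step-disability correlation found here would be a device artefact. The documents do not support that, because a real association is plausible and the error may be small.

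Third, the end-of-dose question is answered within patients, where a constant error cancels. This stands, except for patients whose aid use changes over the cycle. Nor does the point touch sleep or heart-rate measures.

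Fourth, the study is exploratory, broad entry is deliberate, and the article is condensed. The full protocol may record aids, and Analysis strategy already allows subgroups by clinical features. So the missing mention of aids is not itself an error, and excluding these patients is not warranted. But calling results hypothesis-generating does not remove a bias in the correlation that the first aim calls for, and the one safeguard the article states does not cover it.

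**Conclusion.** The point holds as a conditional bias in one family of analyses: pooled, between-patient correlations of step count and distance with disability scores. The article itself establishes the device, the open eligibility and the planned correlation. That the watch loses steps in aid users is a general measurement argument. The share of aid users, the miss rate and the leg grading of INCAT are assumptions.

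At 20% aid users and no true association, the induced correlation lies between about -0.06 and -0.46 for a leg-only score, and between about -0.04 and -0.31 with an arm part, over 10% to 70% missed. If steps truly fall with disability, the error enlarges the association, for example from -0.38 to -0.50 at 30% missed.

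A reader might go further and conclude that the end-of-dose comparison is compromised or that the digital outcomes as a whole are invalid. Neither follows: the first needs aid use to change within the cycle, and the second ignores outcomes that do not depend on counting steps. This is a cheap improvement, not a flaw that undermines the study.

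**What to change.** Keep eligibility and all patients as they are, and add the following:

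1. Record walking-aid and wheelchair use at V1, V2 and V3, and fix one wrist per patient at V1.
2. Keep the pooled step and distance correlations, but report beside them results stratified by, or adjusted for, aid status. Show wheelchair users separately for step and distance outcomes.
3. In the end-of-dose comparison of steps and distance, flag patients whose aid use changes.
4. State that a pooled step-disability correlation will not be read as validity of the watch unless its direction also holds among unaided walkers.

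The unaided group should not replace the pooled analysis. Restricting to it removes the artefact but also narrows the disability range, which halved a true correlation from -0.38 to -0.19 in Step 4.

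**Cost:** one item per visit, one instruction at V1 and some analysis wording, with no new equipment or visits. The downsides are small strata in a cohort of about 60, a narrower score range within them, and a correlation that may look weaker.
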